### Plans to promote participant retention and complete follow-up {18b}

The collection of the data for the primary outcome will be independent of the patient’s cooperation. The information will be provided by the collaborating health insurance companies. Data collection for the secondary outcomes will always be conducted by members of the project team via a personal visit to the patient’s home. Questionnaires will never be sent to patients via mail.

### Data management {19}

Study data are collected via an online electronic data capture system (secuTrial® database) that can be accessed online in a browser-based manner. All collected data are entered directly into the study’s eCRF by the study teams at the centers. An audit trail records the initial entries and any changes made, the time and date of entry, and the username of the person who authorized the entry or change.

The EDC system is accessed via a standard browser on a device connected to the Internet. Password protection ensures that only authorized persons can access the system to view, add, or edit data according to their permissions. Records and documents related to the conduct of this study, including eCRFs, informed consent forms, laboratory test results, and clinical records will be retained for 10 years.

### Confidentiality {27}

A Trust Center is being set up as part of eliPfad. This is located in the study center of the Medical Clinic II for Internal Medicine of the University Hospital Cologne. The persons working there do not participate in any way in the data collection, patient care, or evaluation of eliPfad. The Trust Center is divided into a confidence center and a data management center. Both units are separated from each other in terms of space and personnel.

The confidence center has the non-encoded names, addresses, and the date of enrollment in the project of the patients. This data is needed so that the confidence center can send invitations to individual interviews to patients in the eliPfad project on behalf of the evaluators at the scheduled times.

Name, date of birth, insurance number, and health insurance are required by the confidence center to obtain the insurance billing data from the collaborating statutory health insurance companies. For this purpose, the collaborating health insurers receive from the confidence center a list of their insured persons (name, date of birth, insured person number) with an assigned pseudonym, so that the health insurers can then transmit pseudonymized data to the data management unit. No further data is transmitted to the health insurance companies. For patients who are insured with other statutory health insurance companies, the confidence center requests the patient receipts from their respective health insurance companies. Patient receipts are proof of all individual services financed by the health insurance company. As soon as the patient receipts are available, all personal information is removed and the receipt is given a pseudonym.

To be able to perform these tasks, the confidence center manages the pseudonym keys, i.e., the assignment of the patients’ plain names with address, insurance number, and date of birth to the patients’ pseudonyms used in the project. The electronic storage of the assignment of the pseudonyms to the non-encoded names takes place exclusively on a password-protected stand-alone computer of the trust center, which is located in an access-restricted room.

The second unit in the Trust Center is the data management unit. The main tasks and responsibilities of the data management unit within the trust center are the management of the pseudonymized study and pseudonymized SHI data, as well as the linking of this data and their forwarding to the evaluators.

### Plans for collection, laboratory evaluation, and storage of biological specimens for genetic or molecular analysis in this trial/future use {33}

Urine and blood samples will be collected at A0–A3. Blood samples will be drawn by the case manager or a study nurse of each center. Measurements will be conducted in the laboratory of the respective center.

## Statistical methods

### Statistical methods for primary and secondary outcomes {20a}

The primary analysis set is derived according to the intention-to-treat-principle (treatment policy strategy): All patients who are included in the study and randomized are analyzed in their allocated group. A secondary analysis set is defined according to the hypothetical strategy (per protocol), comprising all included, eligible, and randomized patients who proceed without interruptions (especially transfers) from stationary to ambulant care. The primary null hypothesis is tested using negative-binomial regression of the number of individual readmissions on the group, if it converges to a solution on the collected data, assuming overdispersed data. In case of equidispersion or non-convergence of the negative-binomial regression, Poisson regression is used. Models will include age, sex, study site, offset (log time under risk), and robust variance-covariance estimation (clustered sandwich estimator) (Stata/SE 17.0, StataCorp LLC, College Station, TX, USA; call: poisson/nbreg outcome group, sex age study.site offset(log.time.under.risk) irr vce(cluster patient.id)). Negative-binomial regression is favored if it converges to a solution on the collected data. Other possible confounder will be specified in the SAP after discussion by clinicians and evaluators and variables will be included in the analysis. Time under risk is defined as the time patients spend at home or in a care facility that does not have medical staff on duty. If a patient dies, they will no longer contribute time under risk from this point onwards. In case of underdispersed data a generalized Poisson model is considered, which is capable of dealing with underdispersion. For the main effect group (relative rate reduction), the *p*-value and the associated two-sided 95% confidence interval are determined. The significance level is 5% two-sided.

The regression approach can take into account the shorter time under risk (than 6 months), especially due to loss-to-follow-up or dropout. The main estimator here is the ratio of event rates (defined as the total number of readmissions/sum of risk times) of intervention to the control group.

Secondary analyses models will also include strata and confounder. The frequencies of repeated events like number of rehabilitation services or transfers to acute geriatric units between T1 and T3 (health insurance companies’ data) and time variables like duration of stay in index hospital, intensive care unit, external hospitals, or rehabilitation facilities will be analyzed analogous to the primary endpoint. Patient questionnaire scales will be evaluated by linear mixed models with repeated measurement over time. Time to death will be analyzed by Cox regression.

In general, quantitative target variables are described by the number of valid cases, mean ± standard deviation, and percentiles (0, 25, 50, 75, 100), and qualitative target variables by absolute and relative (%) frequencies, over time.

All details and methods of statistical analysis will be documented in a statistical analysis plan (SAP). The SAP shall be finalized before database closure and will be approved by the two principal investigators and representatives of the evaluating statistics departments.

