#### Time frame of the intervention

Patients are enrolled within two working days after admission to an internal ward (see eligibility criteria above) and the hospital part of eliPfad begins. After discharge from the index hospital stay, patients will be treated in eliPfad for 42 days in the ambulatory setting. This time frame is fixed and will not be prolonged due to planned or unplanned hospital stays within the 42 days. Should the patient be admitted to a hospital within 42 days, the intervention would pause during that period and resume afterward—given that the 42nd day after the initial discharge is not yet reached. A follow-up visit is planned 6 months after the discharge from the index hospital stay.

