### Outcomes {12}

#### Time points, data collection, and outcomes

Four time points (T) are defined which are accompanied by timely scheduled assessments (A). All assessments are carried out by members of the study team in person to ensure the completeness of the data. Pretests of the single questionnaires and the entire data collection assessment were conducted to test duration and feasibility for the patient population. Depending on the visit, these assessments are carried out either in hospital or at the patient’s home:T0/A0: Baseline, immediately after randomization and up to 2 working days after admission to the internal ward (in the hospital).T1: Discharge day from the index hospital stay. A1 can be performed up to 3 days before scheduled discharge (in the hospital) or up to 3 days after T1 (in the patient’s home).T2: End of the intervention phase, 42 days after T1. A2 can be performed up to 5 working days after T2 (in the patient’s home); if A2 cannot take place in this period (hospital admissions, etc.), A2 can still be collected on day 60 at the most, counted from discharge from the index hospitalization.T3: 180 days after T1. A3 can be performed up to 10 working days after T3 (in the patient’s home).

The primary outcome is the number of unplanned rehospitalizations over 180 days after the end of the index hospital stay. Unplanned inpatient readmission is defined as the admission of a previously discharged patient due to unplanned events or deterioration of health that can no longer be treated in the outpatient setting. The rehospitalization frequencies are determined using collaborating health insurance companies’ data. In addition, at A3, the patients are actively questioned by the case manager about possible hospital stays in the last 180 days.

The secondary outcomes are the variables required for the testing of the secondary hypotheses. The variables collected, when they are collected and the type of source are listed below:

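### Patients are randomised and treated in hospital, but deaths and costs are listed only from discharge, and patients with no risk time cannot inform the primary rate ratio

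*Protocol article*

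**What the plan says.** All references are to the protocol article.

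- **Randomisation and start of treatment.** Time points, data collection, and outcomes: "T0/A0: Baseline, immediately after randomization and up to 2 working days after admission to the internal ward". The section on the intervention's time frame adds: "Patients are enrolled within two working days after admission to an internal ward (see eligibility criteria above) and the hospital part of eliPfad begins".
- **Primary outcome and set.** The count is the "number of unplanned rehospitalizations over 180 days after the end of the index hospital stay". For the primary set, Statistical methods {20a} states: "All patients who are included in the study and randomized are analyzed in their allocated group".
- **Primary model.** Negative-binomial or Poisson regression with the log of time under risk as offset. The definition reads: "Time under risk is defined as the time patients spend at home or in a care facility that does not have medical staff on duty". Death ends a patient's risk time. The main estimator is the ratio, between arms, of total readmissions over summed risk time.
- **Deaths.** Secondary hypotheses names overall survival, and {20a} assigns Cox regression to time to death without giving a time origin. The death item in Outcomes {12} is insurer data from T1 to T3, T1 being the day of discharge. Table 1 lists death only at T3/A3. Under Adverse event reporting and harms {22}, control patients need no safety documentation.
- **Costs.** Cost-effectiveness is to be judged from the perspective of the Statutory Health Insurance. The cost sum in Outcomes {12} also runs from T1 to T3. The index stay is recorded as durations (total, intensive or intermediate care, other departments).

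**The concern.** The comparison of arms is protected by randomisation from T0 onwards. Three quantities begin later than that, after part of the intervention has been given: the readmission rate, the listed deaths and the listed costs.

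For costs, a complex in-hospital programme (individual treatment plan, GP involvement, early rehabilitation, case management) could raise or lower the cost of the index stay, and the listed window would not see it. For survival, the deaths closest to the acute illness could be absent from an endpoint called overall survival. For the primary outcome, the plan promises an analysis of everyone randomised, but the model can learn only from patients who accrue risk time. Who accrues it is decided after randomisation and could depend on allocation.

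**Working it through.** **1. The plan's own sample size.** Inputs from Sample size {14}: control distribution 0.35/0.40/0.20/0.05, intervention 0.495/0.331/0.149/0.025, two-sided 5%, power 90%, allocation 1:1.

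N = (1.960 + 1.282)² × (1 − Σ[(p+q)/2]³) / (12 × 0.5 × 0.5 × (P − 0.5)²), with P = 0.5803. This gives 472.8, hence 237 per group and 474 in total, as stated. Then 237/0.5 = 474 per group, 948 randomised, as stated. The means are 0.95 and 0.704, a ratio of 0.741.

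**2. The windows side by side.**

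| Quantity | Starts at | In-hospital phase after randomisation |
|---|---|---|
| Intervention | enrolment, in hospital | included |
| Readmission count and risk time | T1 | outside |
| Insurer death item | T1 | outside |
| Insurer cost sum | T1 | outside |
| Index-stay durations | index stay | included, as days and not as costs |
| Most questionnaires, laboratory values | A0 | included |

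The difference in cost between arms is the difference over T0 to T1 plus the difference over T1 to T3. Only the second term has a listed cost source. For deaths between T0 and T1 no both-arm source is listed. Safety reporting cannot serve, because controls are exempt and, even in the intervention arm, events in the natural course of pre-existing disease are not documented.

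**3. Zero risk time in the primary model.** A patient who dies before discharge, or who moves to other inpatient care and never reaches home or an equivalent setting in the window, has risk time 0, and log(0) is undefined. Section {20a} deals with shorter risk time, not with none.

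A mock trial of 948 patients, with each given a 5% chance of zero risk time, produced 50 such patients. A Poisson fit with group as the only covariate behaved as follows:

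- with the 50 included: the fit failed;
- with the 50 left out: n = 898, rate ratio 0.796;
- with a tiny positive exposure in place of zero: n = 948, rate ratio 0.796.

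These patients therefore carry no information whichever way they are coded.

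**4. Numbers and power.** The share s with zero risk time is not in the documents; 1% to 10% is assumed. Evaluable patients are 474 × (1 − s) × 0.5 in control and 474 × (1 − s) × 0.7 in intervention, using the planned 50% and 30% losses. Power is Φ(|ln 0.741| / SE − 1.96), where SE² = 0.7475/(n₁ × 0.95²) + 0.6564/(n₂ × 0.704²). The variances 0.7475 and 0.6564 follow from the two stated distributions.

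| s | Patients out of 948 | Power |
|---|---|---|
| 0% | 0 | 93.4% |
| 1% | 9 | 93.1% |
| 2% | 19 | 92.9% |
| 5% | 47 | 92.1% |
| 10% | 95 | 90.7% |

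**5. Possible selection effect.** Suppose the intervention has no effect on readmission, in-hospital mortality is c in control and t in intervention, and the extra survivors have r times the average readmission rate. The expected rate ratio is [(1 − c) + (c − t) × r] / (1 − t). All inputs are assumed:

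- c = t = 5%: 1.00;
- c = 5%, t = 3%, r = 2: 0.99/0.97 = 1.02;
- c = 10%, t = 5%, r = 3: 1.05/0.95 = 1.11.

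**The case against.** **On the primary model.** A readmission presupposes a discharge, so a patient who dies in hospital cannot have the outcome. With the estimator defined as readmissions over risk time, such a patient adds zero to both sums, and the ratio is the same with or without them. Everyone with any risk time is analysed as allocated. Every post-discharge readmission endpoint shares this conditioning, and a coding rule for zero offsets is ordinary analysis-plan detail. Most of this stands: the plan does not produce a wrong rate ratio by dropping these patients. What remains is that the set is described as everyone randomised when the estimate is conditional on reaching risk time. The plan also expects transfers, since its secondary set is defined by their absence.

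**On survival.** Overall survival is named without a window and the Cox origin is open, so a survival analysis from randomisation is compatible with the text. The T1 to T3 item belongs to a list of insurer data and does not define the endpoint. A reader might infer that survival is fixed to start at discharge; the documents do not say so. What they lack is a listed source for earlier deaths in both arms.

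**On costs.** Index-stay and intensive-care days are collected and could be valued later, and the article gives no costing method. That is fair, but the cost sum is given a stated window, and that window excludes the index stay.

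**On scale.** Patients with short life expectancy, those predominantly bedridden, nursing-facility residents and those without rehabilitation potential are excluded, which should keep the share with no risk time down.

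**Conclusion.** The point holds and should be corrected, but it does not undermine the trial. Its firmest part is the cost window: as written, the comparison omits the cost of a stay in which part of the intervention is delivered. Next is survival, where deaths between randomisation and discharge have no listed both-arm source and the time origin is unstated. The primary-model part is real but small. At an assumed 1% to 10%, about 9 to 95 of 948 patients contribute nothing, power stays at about 91% to 93%, and the rate ratio is undisturbed when similar patients die in hospital at equal rates. A shift as large as 1.11 needed in-hospital mortality halved and extra survivors with three times the average readmission rate.

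Two stronger readings are not supported. A reader might infer that outcomes in general begin at discharge; most questionnaires and the laboratory values start at A0, and index-stay durations are collected. A reader might also turn the share with no risk time into a share of all deaths that is missed. That group includes living patients who never reach home, and the documents give no mortality figure.

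**What to change.** 1. **Costs:** have the insurer cost data start at the index admission or T0 in both arms, and state that intervention costs are added.
2. **Survival:** analyse overall survival from randomisation in all randomised patients, and record in-hospital deaths with dates in both arms.
3. **Primary model:** describe the set as randomised patients with more than 0 days at risk, analysed as allocated. Report in-hospital deaths and patients never at risk by arm, so that readers can judge selection.
4. **Optional:** a supportive analysis of all randomised patients, such as days alive and out of hospital over a fixed period from T0.

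The cost is an earlier start date in the insurer data specification, collection of in-hospital deaths in both arms, and some wording in the analysis plan, which by {20a} is to be finalised only before database closure. No change in sample size is needed. The price in presentation is that the primary model can no longer be called an analysis of all randomised patients.

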Proactive care is planned based on evidence-based guidelines and enacted both via individualized care plans, monitoring of vital parameters with individual target ranges, and “eliBoards.” The implementation of online “eliBoards” conferences and an electronic patient file allow for close interaction between hospital and GPs, assuring interdisciplinary and cross-sectoral cooperation. Ideally, the GP is involved in the planning of the treatment plan from an early stage on while the patient is still in hospital. This efficient exchange of information aims to ensure that emerging health problems of participating patients are realized and addressed quickly, as shown crucial for successful health care [37]. This form of collaboration between health care sectors using digital means has, to the best of our knowledge, not been done before. After discharge, the developed treatment plan is seamlessly transferred to the ambulatory sector. Patients continue their physiotherapeutic exercises at home and measure relevant vital parameters. The data are captured electronically and transmitted to the patient file in which both a specially trained case manager and GP monitor them on a regular basis. The case manager is furthermore involved in the development of the individual treatment plan and serves as a personal contact for the patients, making the case management a crucial and supporting intersection of patient-centered and proactive care, as shown effective before [19, 22].

eliPfad is expected to lead to an improvement or recovery of the patient’s autonomy and quality of life. Furthermore, an overall reduction of unplanned readmissions to hospitals and rehabilitation measures is expected. The effect of the single components used in eliPfad, i.e., proactive, integrated, and patient-centered care, telemedical support for both patients and caregivers, and extensive physiotherapy across inpatient and outpatient settings, has been proven before. eliPfad uniquely uses these evidence-based intervention components and embeds them in a cross-sectoral complex intervention for frail multimorbid elderly and might therefore improve care of the target population with expected stable costs at the same time.

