### Relevant concomitant care permitted or prohibited during the trial {11d}

The only restriction for patients regarding concomitant care is the use of rehabilitation measures within the intervention period of eliPfad in the ambulatory setting. Patients who clearly state that they want to participate in rehabilitation measures before the 42nd day after discharge are not eligible for eliPfad (see “Eligibility criteria”). The reason is that eliPfad aims at reducing the number of rehabilitation measures because participating in eliPfad is considered to be a rehabilitation measure itself.

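### The secondary analysis set is labelled a hypothetical strategy but keeps only patients whose move out of hospital was not interrupted, so it does not estimate that estimand and loses the protection of randomisation

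*Protocol article*

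**What the plan says.** The statistical methods section {20a} of the protocol article names two analysis sets. The primary one is intention-to-treat with a treatment policy strategy: every randomised patient is analysed in the allocated arm. The other is introduced as follows: "A secondary analysis set is defined according to the hypothetical strategy (per protocol), comprising all included, eligible, and randomized patients who proceed without interruptions". The sentence ends by saying what counts as uninterrupted: patients "who proceed without interruptions (especially transfers) from stationary to ambulant care".

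The order of events is fixed elsewhere. The baseline assessment is described as "Baseline, immediately after randomization and up to 2 working days after admission to the internal ward". The part of section {11a} on timing adds: "Patients are enrolled within two working days after admission to an internal ward (see eligibility criteria above) and the hospital part of eliPfad begins". The move to ambulatory care follows later.

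The intervention description {11a} gives the case manager the task of coordinating the continuation of care from hospital to home. The outcomes section {12} lists transfers to external hospitals and to rehabilitation facilities among the data collected, and Table 1 schedules both at T1, the discharge time point. The models in {20a} contain age, sex, study site and an offset. Further confounders are left to the SAP.

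**The concern.** The label and the definition answer different questions. A hypothetical strategy asks what the readmission rate would have been in all randomised patients had no interruption occurred. The stated set compares the patients in each arm who had none. The two agree only if, given arm and the model covariates, patients with and without an interruption have the same expected outcome.

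That condition is hard to accept here. Patients who need a transfer out of the index stay are plausibly sicker, and age, sex and site capture little of that. Treatment has already begun when the interruption happens, the trial is open-label, and organising the transition is part of what the intervention arm receives. If eliPfad changes who is interrupted, the retained patients differ in prognosis between arms, and randomisation no longer protects the comparison.

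At stake is the interpretation of the only analysis set named besides the primary one. Under its present label, a result could be taken as the effect of eliPfad had care run without interruption, and could seem to support or weaken the primary result for reasons of selection alone.

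**Working it through.** **1. The plan's own figures.** From the sample size section {14}:
- Control mean: 0.40×1 + 0.20×2 + 0.05×3 = 0.95.
- Intervention mean: 0.331×1 + 0.149×2 + 0.025×3 = 0.704.
- Ratio: 0.704/0.95 = 0.741, a 25.9% reduction, as stated.

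The article gives no transfer or interruption rate, so everything below rests on assumed inputs.

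**2. Label against definition.**

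| | Hypothetical strategy | Set defined in {20a} |
|---|---|---|
| Population | all randomised | those not interrupted |
| Interrupted patients | outcome estimated as if uninterrupted | removed |
| Valid under | a stated assumption and a method | ignorability given the covariates |

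**3. Graded dependence (assumed).** One frailty score u ~ N(0,1) drives both readmission and transfer.
- Readmissions are Poisson with mean 0.95·exp(0.6u − 0.18) in both arms, so the true ratio is 1.00.
- The log odds of transfer are a + u, plus log(OR) in the intervention arm, with a = logit of 0.1, 0.2 or 0.3.
- Transferred patients are dropped from both arms. The result is the unadjusted ratio of mean counts, with 2,000,000 simulated patients per scenario.

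| Control transfer rate | OR 1 | OR 0.7 | OR 0.5 |
|---|---|---|---|
| about 13% | 0.996 | 1.021 | 1.036 |
| about 24% | 1.000 | 1.032 | 1.050 |
| about 33% | 0.996 | 1.032 | 1.059 |

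With equal transfer odds in the two arms, the null ratio stays at about 1.00. With odds lowered by 30% to 50%, it is about 1.02 to 1.06. A true 0.741 would then appear as 0.741×1.02 = 0.76 to 0.741×1.06 = 0.79.

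**4. Extreme case (assumed).** 20% of patients are high risk, with twice the rate L of the rest, and every exclusion comes from that group.
- Low-risk rate: 0.8L + 0.2×2L = 1.2L = 0.95, so L = 0.792 and the high-risk rate is 1.583.
- Controls, 20% excluded (all of the high-risk patients): retained mean 0.792.
- Intervention, 10% excluded (half of them), no true effect: (0.8×0.792 + 0.1×1.583)/0.9 = 0.880.
- Null ratio: 0.880/0.792 = 1.11. A true 0.741 appears as 0.741×1.11 = 0.82.
- With the exclusions reversed: 0.792/0.880 = 0.90.

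**The case against.** The strongest reply is that {20a} defines a set, not an estimator. Fitting an adjusted or weighted model to uninterrupted patients is one way to target a hypothetical estimand if interruption is ignorable. The article leaves further confounders and all method details to the SAP, and {20c} already foresees multiple imputation with departures from missing at random. It is right that missing weighting detail is no fault in an article. But the article itself fixes both the label and the restriction to uninterrupted patients, and details added later do not make the two agree.

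Some stronger readings are tempting and not supported:

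- **That the plan means to reduce the excluding event.** It says "eliPfad aims at reducing the number of rehabilitation measures because participating in eliPfad is considered to be a rehabilitation measure itself" and that "an overall reduction of unplanned readmissions to hospitals and rehabilitation measures is expected". Both concern rehabilitation measures, and the second also unplanned readmissions. No direction is stated for transfers out of the index stay, and patients who want rehabilitation on days 1 to 42 are not eligible in either arm. What the text supports is that the intervention could affect the handover.
- **That the excluding event is the secondary outcome** "transfers to acute geriatric units between T1 and T3". That outcome is counted after discharge. The exclusion concerns the handover from the index stay. The transfers scheduled at T1 in Table 1 are the nearer match.
- **That the result will be biased, by about 11%.** The 1.11 needs every high-risk control, and no low-risk control, to be removed. Bias is a risk whose size and direction the article does not determine.
- **That exclusions fall on the intervention arm only.** The same simulation would then give a null ratio of 0.82 to 0.95, but the definition covers all randomised patients.

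It also stands that the set is secondary and that the primary analysis does not depend on it.

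**Conclusion.** The point holds as a mismatch between label and definition, with a structural risk of selection bias. The subset selects on an event after randomisation that is plausibly prognostic and that an open-label intervention could influence. It estimates the named strategy only if interruption is ignorable given the covariates, and the covariates stated in the article make that doubtful.

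The size cannot be fixed from the article. The null ratio of about 1.00 requires that transfer depends on prognosis alike in both arms. The range 1.02 to 1.06 rests on the assumed frailty model without covariate adjustment. The values 1.11 and 0.90 mark an extreme case, not an expectation. Severity is low to moderate.

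**What to change.** Choose one of two changes, in the SAP and in any restatement of {20a}.

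(a) Call the set per-protocol, drop the hypothetical-strategy label, and report the result as supportive only, not as the effect that would be seen without interruptions. This costs a change of wording.

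(b) Keep the hypothetical estimand for all randomised patients. Estimate it either by weighting the uninterrupted patients by the inverse of their probability of remaining uninterrupted, or by multiply imputing readmission counts for the interrupted ones. Use baseline MPI, age, sex, site and index diagnosis, and state the assumption of no unmeasured confounding. Simply censoring at the transfer would not do: the primary outcome is counted from the end of the index stay, so a patient transferred before then contributes no follow-up.

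The baseline variables for (b) are already available, since MPI and the index diagnoses are part of the eligibility check. The cost is modest programming and one more modelling assumption. The SAP is to be finalised before database closure, so either change can be made there.
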